## Abstract

**Background:**

Acute pancreatitis is mostly caused by gallstones or sludge. Early decompression of the biliary tree by endoscopic retrograde cholangiography (ERC) with sphincterotomy may improve outcome in these patients. Whereas current guidelines recommend early ERC in patients with concomitant cholangitis, early ERC is not recommended in patients with mild biliary pancreatitis. Evidence on the role of routine early ERC with endoscopic sphincterotomy in patients without cholangitis but with biliary pancreatitis at high risk for complications is lacking. We hypothesize that early ERC with sphincterotomy improves outcome in these patients.

**Methods/Design:**

The APEC trial is a randomized controlled, parallel group, superiority multicenter trial. Within 24 hours after presentation to the emergency department, patients with biliary pancreatitis without cholangitis and at high risk for complications, based on an Acute Physiology and Chronic Health Evaluation (APACHE-II) score of 8 or greater, Modified Glasgow score of 3 or greater, or serum C-reactive protein above 150 mg/L, will be randomized. In 27 hospitals of the Dutch Pancreatitis Study Group, 232 patients will be allocated to early ERC with sphincterotomy or to conservative treatment. The primary endpoint is a composite of major complications (that is, organ failure, pancreatic necrosis, pneumonia, bacteremia, cholangitis, pancreatic endocrine, or exocrine insufficiency) or death within 180 days after randomization. Secondary endpoints include ERC-related complications, infected necrotizing pancreatitis, length of hospital stay and an economical evaluation.

**Discussion:**

The APEC trial investigates whether an early ERC with sphincterotomy reduces the composite endpoint of major complications or death compared with conservative treatment in patients with biliary pancreatitis at high risk of complications.

**Trial registration:**

Current Controlled Trials ISRCTN97372133 (date registration: 17-12-2012)

**Electronic supplementary material:**

The online version of this article (doi:10.1186/s13063-015-1132-0) contains supplementary material, which is available to authorized users.

## Background

Acute pancreatitis is a leading cause for acute hospitalization [1]. In most cases, pancreatitis results from gallstones causing obstruction of Vater’s ampulla [2, 3]. As biliary stones or sludge is thought to initiate and aggravate pancreatitis, early biliary decompression – achieved by endoscopic retrograde cholangiography (ERC) with sphincterotomy – may ameliorate the disease course [4, 5]. In return, ERC with sphincterotomy itself may also be associated with complications in up to 10 % of patients [6, 7].

Several studies have investigated the effect of routine ERC in biliary pancreatitis [8]. Guidelines state an undisputed indication for ERC in patients with concurrent cholangitis and pancreatitis [2, 9]. In patients with mild disease, early ERC is not indicated because in these patients the risk for complications does not outweigh the potential benefit [2, 9].

Recent guidelines advise to perform ERC with sphincterotomy in case of pancreatitis with cholestasis, but acknowledge the moderate quality of evidence for this recommendation [2, 9]. For those patients with pancreatitis and at high risk for developing complications (that is, predicted to be severe) without cholangitis, data are conflicting. A meta-analysis found no beneficial effect of routine early ERC compared with conservative treatment [8]. However, the studies have notable shortcomings that preclude reliable recommendations on the use of ERC in patients with predicted severe biliary pancreatitis without cholangitis [10]. First, patients included were those with a low pre-likelihood of a biliary etiology, those at low risk for developing complications (that is, predicted to be mild), and those with cholangitis at presentation. Second, patient selection criteria and study endpoints (complications) varied considerably between studies and also included clinically less relevant complications such as pleural effusion or ascites. Third, the trials did not present data separately regarding liver biochemical tests, an omission that precludes performing a subgroup analysis for patients with cholestasis. Fourth, routine “early” ERC was performed during a wide time frame (48 to 72 hours after admission), which may be too late to prevent complications from severe disease or increase the risk for ERC-related complications. Fifth, the trial protocols did not specify precisely when the sphincterotomy should be performed. This resulted in many patients who underwent ERC without sphincterotomy. We believe sphincterotomy should routinely be performed during ERC to decompress the biliary duct, even in the absence of gallstones or visible sludge in the common bile duct [11–13]. Sixth, no criteria were set to guarantee that ERCs were performed by experienced endoscopists, although ERC is an intervention that requires considerable training and expertise [14, 15]. Finally, even if the data of all the available randomized trials are pooled, such analysis will still not have sufficient power to detect clinically relevant and statistically significant effects of early ERC with sphincterotomy on major complications or death in patients with predicted severe biliary pancreatitis without cholangitis [8, 16].

The APEC trial is designed to investigate whether early ERC with sphincterotomy compared with conservative treatment improves outcome in patients with biliary pancreatitis without cholangitis who are at high risk for complications.

## Methods/Design

The APEC trial is a randomized controlled, parallel group, superiority, multicenter trial. Patients with acute pancreatitis will be assessed for study eligibility within 24 hours after presentation to the emergency department. Patients with biliary pancreatitis without cholangitis and at high risk of developing severe disease are eligible for randomization. Patients are randomized to early ERC with sphincterotomy or to conservative treatment (see Additional file 1: Figure S1 and Additional file 2: Figure S2). Blinding of the patients and physicians for either treatment (ERC or conservative treatment) is unfeasible. The trial will be conducted in 27 hospitals of the Dutch Pancreatitis Study Group. The APEC trial protocol is in accordance with the Spirit Guidelines [17].

### Primary endpoint

The primary endpoint is a composite of major complications or death occurring within 180 days after randomization (that is, the composite endpoint can only occur once per patient). Major complications are defined as persistent organ failure, pancreatic necrosis, bacteremia, cholangitis, pneumonia, and pancreatic endocrine or exocrine insufficiency (see Additional file 3: Table S1 for definitions).

### Secondary endpoints

The secondary endpoints are as follows:“Per protocol” analysis of the primary endpoint“As treated” analysis of the primary endpointIndividual components of the primary end pointMultivariable analysis of the primary endpoint in case of significant differences in baseline variablesInfected necrotizing pancreatitisNeed for new intensive care unit admissionLength of stay at intensive care unitERC-related complications (see Additional file 4: Table S2 for definitions [39-41] )Cholangitis during admission Number of endoscopic, radiological, and operative (re-)interventions Readmission for biliary events (recurrent acute biliary pancreatitis, cholecystitis, biliary colics, or cholangitis) Difficulty of cholecystectomy (as scored by Visual Analog Scale 1 to 10) Quality of life (Short Form-36 and EQ5D-5 L) including quality adjusted life years (QALY) Direct medical costs and direct and indirect nonmedical costs

### Inclusion criteria

Inclusion criteria are as follows:Acute pancreatitis, which is defined as the presence of at least two out of the following three criteria: 1) pain in the upper abdomen, 2) serum amylase or lipase concentration > 3 times the upper limit of normal, or 3) imaging features of acute pancreatitis on computed tomography (CT) or magnetic resonance imaging (MRI) [18].High risk of developing severe disease (that is, predicted to be severe) based on either one of the following criteria: Acute Physiology and Chronic Health Evaluation (APACHE II score) ≥ 8 [19] (see Additional file 5: Table S4), 2) Modified Glasgow score ≥ 3 [20] (see Additional file 6: Table S3), or 3) C-reactive protein > 150 mg/L [21, 22].High probability of a biliary etiology based on at least one of the following criteria: 1) gallstones or biliary sludge on imaging (any type), 2) dilated common bile duct on imaging defined as > 8 mm in patients ≤ 75 years or > 10 mm in patients > 75 years, 3) alanine aminotransferase (ALAT) > two times the upper limit of normal (no absolute numerical value is chosen because of the multicentric design with varying upper limits among hospitals and sex-based differences in the upper limit of normal values [23–25]).Ability to perform ERC within 24 hours after presentation to the emergency department and no more than 72 hours after symptom onset.In case of a previous episode of necrotizing pancreatitis, patient should be fully recovered (confirmed on imaging).Age ≥18 years.Written informed consent.

### Exclusion criteria

The exclusion criteria include the following:Cholangitis (see Additional file 3: Table S1 for definition).Pancreatitis due to other causes such as alcohol abuse (more than 4 units per day), metabolic causes (hypertriglyceridemia or hypercalcemia), medication, trauma, etc.Previous pancreatic sphincterotomy or needle knife precut.Chronic pancreatitis (see Additional file 7: Table S5 for definition).International Normalized Ratio that cannot be corrected to less than 1.5 with clotting factors or fresh frozen plasma.Pregnancy.

### Randomization

Patients are randomized to early ERC with sphincterotomy or to conservative treatment (1:1 ratio) with a web-based randomization module (ALEA, Academic Medical Center, Amsterdam, The Netherlands) in random blocks of two, four or six. At randomization, patients are stratified according to the presence of cholestasis and for region of the hospital. Cholestasis is defined as a serum bilirubin > 40 μmol/L at randomization or a dilated common bile duct (defined as > 8 mm in patients ≤ 75 years or > 10 mm in patients > 75 years).

### Treatment protocol

#### Early ERC with sphincterotomy

Early ERC with sphincterotomy is performed within 72 hours after symptom onset and within 24 hours of hospital admission. A sphincterotomy is always performed irrespective of the presence of the common bile duct stones. ERC is performed by or under the direct supervision of an experienced endoscopist, which defined as a person who has done more than 400 ERCs in his or her lifetime and has performed more than 50 ERCs yearly on average in the previous 3 years. When unable to cannulate the common bile duct, even after precut sphincterotomy, the ERC procedure will be ended, and the patient will be treated conservatively. After the patient has recovered from the acute pancreatitis attack, a repeat ERC is scheduled to perform a full sphincterotomy. According to the intention-to-treat principle, these patients will be analyzed according to their original treatment allocation, that is, early ERC with sphincterotomy. In the case of incomplete stone extraction, a plastic endoprosthesis is inserted, and an elective ERC is scheduled. Antibiotics are only administered in case of contrast injection without adequate biliary drainage.

#### Conservative treatment

Patients in the conservative group are managed according to the conservative supportive treatment regimen for patients with acute biliary pancreatitis as described in the paragraph below. A rescue ERC is performed when a patient develops cholangitis (see Additional file 3: Table S1 for definition). Whenever the attending physician is in doubt concerning whether or not an ERC should be performed, the study coordinator presents the case to an expert panel. This expert panel, consisting of an independent gastroenterologist and a gastrointestinal surgeon, provides a treatment advice within 24 hours. Retained bile duct stones are removed during an elective ERC when the patient is recovered from the initial pancreatitis episode.

### General treatment regimen

Both groups are treated with intravenous infusion of fluids to ensure adequate hydration and diuresis, appropriate analgesic treatment, enteral nutrition if necessary, treatment of endocrine and exocrine pancreatic insufficiency, and a gastric tube in case of vomiting. No antibiotic prophylaxis is given. The treating physician assesses whether the patient requires intensive care monitoring or further supportive measures (for example, mechanical ventilation). All patients will undergo a contrast-enhanced CT (CECT) 5 to 7 days after hospital admission for an assessment of pancreatic necrosis. If a patient recovers quickly and is discharged within 5 days, a routine CECT will not be performed, and the disease will be considered mild. Readmission within 10 days after the initial discharge for complications related to pancreatitis is regarded as a primary admission. The timing of the cholecystectomy is determined by the treating physician depending on the patient’s condition and outcome of the pancreatitis.

### Data collection

Clinical data are collected using case record forms. At all sites, an independent monitor, unblinded to the treatment allocation, will assess the study forms, including the informed consent documents, and compare these with source documents. The in-hospital utilization of healthcare will be registered as part of the data collection. Out-of-hospital use of healthcare will be documented by self-administered questionnaires.

### Follow-up

After hospital discharge, patients are seen at the outpatient clinic and further monitored at the discretion of the physician. After 1, 3, and 6 months, patients will receive a questionnaire (SF-36, SF-HLQ, and EQ5D-5 L, respectively) [26, 27]. A visit is scheduled at 3 months after randomization to identify persistent common bile duct stones or to detect endocrine or exocrine pancreatic insufficiency (serum liver and glucose measurements and fecal elastase).

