#### Additional analyses

Predefined subgroup analysis will be done according to the presence of cholestasis. Logistic regression models will be used to test whether treatment effects differ significantly between these subgroups. Secondary endpoints will be compared using the Pearson’s chi-squared test or Mann-Whitney U test. Additionally, secondary endpoints will be analyzed separately using Cox regression analysis censoring patients no longer at risk and categorizing missing data as no event. For all other analyses, data will be considered missing at random. To evaluate differences in systemic inflammatory response after randomization, the APACHE-II, C-reactive protein levels, and presence of SIRS from randomization to day 7 will be calculated and compared between the treatment groups. To gain further insight into factors that are predictive of major complications or death after ERC, an exploratory analysis of the effects of (essential) baseline covariates (and potential interactions) will be performed using logistic regression analysis. The essential baseline covariates that will be studied are demographics, comorbidity, predicted severity prior to randomization, presence of organ failure prior to randomization, cholestasis, and duration of symptoms prior to randomization. In addition, the time between the start of symptoms and the ERC will be studied.

Direct medical and nonmedical costs and indirect costs will be compared to assess costs per patient with poor outcome (death or severe complications). Validated questionnaires will be analyzed to assess differences in the quality of life and provide input to compare costs per quality-adjusted life year (QALY). Health utility scoring algorithms for the EQ5D-5 L health status profiles available from the literature, based on preferences in the general population using time trade-off elicitation techniques, will be used to derive a QALY estimate for each patient. This QALY will be calculated as the product sum of health utilities and the lengths of the periods between the successive measurements [30, 31].

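### The questionnaire schedule, read literally, gives one EQ5D-5L measurement, but the QALY formula needs several; two related economic rules also need rewording

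*Protocol article*

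**What the plan says.** Four places in the protocol article bear on this.

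- **Follow-up** sets the schedule: "After 1, 3, and 6 months, patients will receive a questionnaire (SF-36, SF-HLQ, and EQ5D-5 L, respectively".
- **Secondary endpoints** lists "Quality of life (Short Form-36 and EQ5D-5 L) including quality adjusted life years (QALY") and, as a separate item, "Direct medical costs and direct and indirect nonmedical costs".
- **Additional analyses, economic paragraph.** Published scoring algorithms for the EQ5D-5L profiles "will be used to derive a QALY estimate for each patient", and the "QALY will be calculated as the product sum of health utilities and the lengths of the periods between the successive measurements". Direct medical, nonmedical and "indirect costs will be compared to assess costs per patient with poor outcome", where poor outcome means death or severe complications. Costs per QALY are planned as well.
- **Additional analyses, first paragraph** gives the general rule: "Secondary endpoints will be compared using the Pearson’s chi-squared test or Mann-Whitney U test".

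The Discussion undertakes to inform on cost-effectiveness and on how much could be saved.

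**The concern.** Three times and three instruments are joined by a word that pairs them in order: SF-36 at month 1, SF-HLQ at month 3, EQ5D-5L at month 6. The utilities come from EQ5D-5L alone, and the QALY rule needs at least two of them per patient. If the schedule were followed as printed, a listed secondary endpoint and one of the two planned cost ratios could not be produced. A form not sent at month 1 or 3 cannot be recovered later.

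The rest of the economic plan raises two smaller questions. A saving is a difference in mean cost, which a rank test does not estimate. And a ratio with the number of poor outcomes in the denominator grows when poor outcomes are prevented, if it is calculated arm by arm.

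**Working it through.** **Design figures.** The article gives no figure for the economic evaluation. The rates used below are those of the sample size calculation: 48% on conservative treatment and 30% with early ERC. They reproduce the stated total. With two-sided alpha 5%, power 80%, 1:1 allocation and no continuity correction, n per arm = [1.960·√(2·0.39·0.61) + 0.842·√(0.48·0.52 + 0.30·0.70)]² / 0.18² = 114.1, so 115 per arm and 230 in total. Then 230/0.99 = 232.3, against 232 stated. Nothing below changes this number.

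**1. QALY.** With measurements at times t₁ < … < t_k, the stated rule sums utility × length of period over k − 1 periods.

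- Follow-up read literally: EQ5D-5L at month 6 only, k = 1, periods = 0. The sum has no terms.
- EQ5D-5L at months 1, 3 and 6: k = 3, two periods, and the sum can be formed.

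To show what a single late value could hide, assume utilities at months 0/1/3/6 of 0.30/0.75/0.85/0.85 in one arm and 0.30/0.60/0.78/0.85 in the other. These are illustrative and not from the article. Averaging the utilities at the two ends of each period:

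| Data used | Arm A | Arm B | Difference |
|---|---|---|---|
| Months 0, 1, 3, 6 | 0.390 | 0.356 | 0.033 |
| Months 1, 3, 6 | 0.346 | 0.319 | 0.027 |
| Month 6 value applied to the half-year | 0.425 | 0.425 | 0 |

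The three-point schedule keeps most of the difference. The single value loses it in this example because the arms have converged by month 6.

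**2. Cost ratio.** Let the mean cost per patient be C in both arms.

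- Ratio per arm, conservative: C/0.48 = 2.08C.
- Ratio per arm, early ERC: C/0.30 = 3.33C.
- Relative size: 0.48/0.30 = 1.6. C cancels, so the factor depends only on the planned rates and on equal mean cost.
- Incremental form: (mean cost ERC − mean cost conservative)/(0.48 − 0.30) = 0/0.18 = 0, which correctly shows outcomes averted at no extra cost.

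**3. Ranks against means.** Assume log-normal costs with median 25,000 (log-SD 0.8) in patients with a poor outcome and median 6,000 (log-SD 0.4) in the others, at the planned rates, plus a fixed extra cost for every ERC patient. None of these costs is from the article. Simulating 200,000 patients per arm gives:

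| Extra cost, ERC | Mean ERC | Mean conservative | P(ERC patient costs more) |
|---|---|---|---|
| 1,500 | about 16,400 | about 19,900 | 0.50 |
| 3,000 | about 17,900 | about 19,900 | 0.56 |

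In the second row early ERC is cheaper on average by about 2,000 while the ranks point the other way. This shows only that the two comparisons can disagree; how far they would in this trial is unknown.

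**The case against.** The strongest reply is that the schedule is a slip. The QALY rule speaks of successive measurements and so presupposes repeated EQ5D-5L, and the literal schedule would also leave SF-36 measured only once. That is persuasive about intent. A reader might infer that EQ5D-5L really is collected once and that the QALY is lost; the article does not show that. What stands is that Follow-up is the only place that gives the schedule, and as printed it contradicts the analysis.

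On the rank test, the article never says outright that costs go to Mann-Whitney. The economic paragraph names no test, and the general sentence cannot cover the whole list of secondary endpoints, which includes per-protocol, as-treated and multivariable analyses. A rank test also does not prevent mean costs from being reported. So it would be too strong to say that costs will be judged by ranks. What stands is that costs and QALYs are on that list, no other comparison is named for them, and the one named does not estimate a saving.

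On the cost ratio, the wording could be shorthand for an incremental ratio, or could mean the average cost among patients with a poor outcome. Neither gives the factor of 1.6, and cost per QALY is planned too. It does not follow that the analysis would penalise the better arm, only that the wording permits a version that does.

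A reader might also object that no baseline utility and no utility for death are given. A condensed article may leave both to the full protocol or an economic analysis plan, so their absence here is not an error.

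**Conclusion.** The contradiction between Follow-up and Additional analyses holds: read literally, zero periods are available for the QALY sum, so the QALY and the cost per QALY cannot be computed as written. This rests on the text alone.

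The other two points hold as requests to tighten wording. The factor of 1.6 assumes a ratio per arm, the planned 48% and 30%, and equal mean cost. The mismatch between a rank test and a promised saving assumes that the general sentence on secondary endpoints applies to costs. The stronger conclusion, that the economic results are unobtainable or misleading whatever was intended, is not supported.

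Only secondary economic endpoints are affected. The primary endpoint, its test and the 232 patients are untouched.

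**What to change.** 1. **Follow-up:** state that EQ5D-5L, with SF-36 and SF-HLQ, is sent at 1, 3 and 6 months. If that is already the practice, the cost is one sentence. If EQ5D-5L is in fact sent once, add it at months 1 and 3, which means two short extra forms per patient. The article reports 144 of 232 randomized, leaving 232 − 144 = 88 still to enter, so an early correction matters; forms missed by patients already past those times cannot be recovered.
2. **Additional analyses, general sentence:** exempt costs and QALYs from the chi-squared/Mann-Whitney rule and compare them as differences in means with bootstrap 95% confidence intervals. The cost is wording only.
3. **Additional analyses, economic paragraph:** replace costs per patient with poor outcome by incremental cost per poor outcome averted, alongside incremental cost per QALY gained. The cost is wording only.

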### Statistical considerations

#### Sample size calculation

The sample size calculation is based on a recent Dutch multicenter observational study of patients with biliary pancreatitis at high risk for complications [11]. The primary endpoint occurred in 32 % of the patients in which ERC was performed compared with 46 % of the patients who were treated conservatively. Taking into account that ERC was not always performed within 24 hours and that sphincterotomy was not routinely performed, a correction factor of 2 % for both percentages is added to both incidence rates. The APEC trial is a superiority trial in which the sample size calculation is based on the assumption that early ERC with sphincterotomy reduces the incidence of the primary endpoint by 18 % (48 % to 30 %). With a power of 80 %, a two-sided significance level of 5 % and a 1 % drop-out rate, a total of 232 patients are required to be included in the study (http://www.stat.ubc.ca/~rollin/stats/ssize/b2.html, accessed 20 July 2015)).

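### As worded, the follow-up schedule collects EQ5D-5L only at 6 months, but the QALY rule needs successive EQ5D-5L measurements, so the QALY cannot be computed from the stated schedule

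*Protocol article*

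**What the plan says.** Four places in the protocol article bear on this.

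- **Follow-up** sets the schedule: "After 1, 3, and 6 months, patients will receive a questionnaire (SF-36, SF-HLQ, and EQ5D-5 L, respectively". A clinic visit at 3 months is also described, for retained stones and pancreatic insufficiency. No questionnaire is attached to it.
- **Secondary endpoints** lists "Quality of life (Short Form-36 and EQ5D-5 L) including quality adjusted life years (QALY", abbreviation included, and lists costs as a separate item.
- **Additional analyses** says where the utilities come from, "Health utility scoring algorithms for the EQ5D-5 L health status profiles available from the literature", and that these "will be used to derive a QALY estimate for each patient". It then gives the formula: "This QALY will be calculated as the product sum of health utilities and the lengths of the periods between the successive measurements". The questionnaires are also to "provide input to compare costs per quality-adjusted life year (QALY", which makes cost per QALY a planned analysis.
- **Data collection** adds only this: "Out-of-hospital use of healthcare will be documented by self-administered questionnaires". It gives no dates.

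No section mentions EQ5D-5L at baseline or at any time other than the one in Follow-up.

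**The concern.** The word *respectively*, together with the singular *questionnaire*, pairs each instrument with one date: SF-36 at month 1, SF-HLQ at month 3, EQ5D-5L at month 6. The QALY formula needs utilities at two or more dates for the same patient, because it multiplies utilities by the time between measurements. The article therefore states a data schedule and a calculation rule that cannot both be followed.

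What is at stake is the QALY endpoint and the cost-per-QALY comparison built on it. The Abstract lists an economic evaluation among the secondary endpoints, and the Discussion promises insight into cost-effectiveness. If the literal schedule were used and the 6-month utility put in place of a QALY, any difference between the arms that had closed by month 6 would not be seen.

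**Working it through.** The article gives no QALY figure to reproduce. Its one reproducible design figure, the sample size, does not depend on this point. For 48 % against 30 %, 80 % power and two-sided 5 %, the standard formula gives 115 per arm, 230 in total. Dividing by 0.99 for drop-out gives 232.3, against the stated 232.

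**Inputs**

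- Measurement dates: Follow-up.
- Source of utilities: EQ5D-5L only (Additional analyses). No SF-36-based utility is planned, so the month-1 SF-36 cannot supply a term.
- Formula: QALY = Σ uᵢ × (tᵢ₊₁ − tᵢ), where the tᵢ are successive EQ5D-5L dates and uᵢ is the utility assigned to each period. Whether that utility is the start value, the end value or the mean of the two does not affect the count below.

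**Count of terms.** With k measurements there are k − 1 periods between successive measurements.

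| Reading of the schedule | EQ5D-5L dates (months) | Measurements | Periods | Months covered |
|---|---|---|---|---|
| As worded | 6 | 1 | 1 − 1 = 0 | 0 of 6 |
| EQ5D-5L at every date | 1, 3, 6 | 3 | 3 − 1 = 2 | (3 − 1) + (6 − 3) = 5 of 6 |

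On the first line the sum is empty. On the second it can be applied, except to the first month, whose valuation is a separate matter that a fuller plan may settle.

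**Illustration of what one utility can miss.** The article gives no utilities, so these are assumed. At 0, 1, 3 and 6 months, arm A has 0.20, 0.75, 0.85, 0.88 and arm B has 0.20, 0.60, 0.80, 0.88.

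- *Months 1 to 6 only, mean of the two ends of each period.*
  - A: 0.80 × 2/12 + 0.865 × 3/12 = 0.1333 + 0.2163 = 0.350.
  - B: 0.70 × 2/12 + 0.84 × 3/12 = 0.1167 + 0.2100 = 0.327.
  - Difference 0.023.
- *Months 0 to 6, with the assumed baseline and the same rule.*
  - A: 0.475 × 1/12 + 0.350 = 0.389.
  - B: 0.400 × 1/12 + 0.327 = 0.360.
  - Difference 0.029.
- *Months 0 to 6, each value carried back over the preceding period.*
  - A: 0.75 × 1/12 + 0.85 × 2/12 + 0.88 × 3/12 = 0.424.
  - B: 0.60 × 1/12 + 0.80 × 2/12 + 0.88 × 3/12 = 0.403.
  - Difference 0.021.
- *6-month value applied to the whole half year.*
  - A and B: 0.88 × 6/12 = 0.440.
  - Difference 0.

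Under these assumptions a difference of 0.021 to 0.029 QALY becomes 0. This shows how the loss would arise. It does not estimate the loss in this trial.

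**The case against.** The strongest reply is that this is a slip of wording. The QALY formula presupposes repeated EQ5D-5L, and Secondary endpoints names SF-36 and EQ5D-5L together. The natural intention is one package of questionnaires sent at all three dates, with *respectively* misplaced. The article also condenses a full protocol, where the schedule would normally be set out.

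Much of this stands. A slip is more likely than a deliberate single measurement, and nothing shows that data were lost. But the article does not leave the schedule to another document. It states one, and that schedule conflicts with its own formula.

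A second reply is that the 6-month utility could be applied to the whole half year, or that missing values are covered by the missing-at-random statement in Additional analyses. The first is a different rule from the one stated, because randomization is not an EQ5D-5L measurement. The second does not help either. If the instrument was not sent at months 1 and 3, no patient has a value at those dates from which others could be estimated.

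A reader might also infer more than the article supports:

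- *SF-36 would lose its course over time.* No section plans one. Additional analyses speaks only of differences in quality of life, which one measurement can address.
- *A single SF-HLQ would have to carry the productivity costs.* The article does not say what SF-HLQ supplies. It appears only in Follow-up.
- *The early months are where the arms would differ most.* This may be reasonable, but the article gives no figure for it.

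**Conclusion.** The point holds as an internal contradiction. From the schedule as stated, EQ5D-5L is measured once, no period between measurements exists, and neither the QALY endpoint nor the cost-per-QALY comparison can be computed by the stated formula. This rests on the ordinary meaning of *respectively* and on EQ5D-5L being the only source of utilities named.

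The reach is limited. Only the QALY and the cost-utility analysis are affected. The primary endpoint and the sample size of 232 are untouched. Cost per QALY is an analysis described under Additional analyses, whereas the listed secondary endpoints are the QALY and the costs. A reader might conclude that the trial actually collected EQ5D-5L only once, or that the QALY endpoint should be withdrawn for some patients. The article supports neither: it does not show what was sent, and a patient without repeated values is a matter for reporting.

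**What to change.** 1. Reword the Follow-up sentence so that EQ5D-5L is given at each of 1, 3 and 6 months, in line with the formula under Additional analyses, and give the time points of SF-36 and SF-HLQ explicitly.
2. Check that the questionnaires actually mailed match the corrected text.
3. If EQ5D-5L was in fact sent only at 6 months to patients already past months 1 and 3, report that their QALY cannot be obtained by the stated formula, and describe the 6-month utility as a comparison at a single time point.

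If the wording is the only error, the cost is one sentence and a check of the mailings. If the literal schedule was followed, the cost for later patients is adding EQ5D-5L to mailings that already exist. Trial status reports 144 of 232 patients randomized (62 %), leaving 88 still to be recruited. Month-1 and month-3 values not collected from those already past these dates cannot be recovered, so the check should be made promptly. The article does not say how many of the 144 are past them.
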